# Protocol of a randomized, double-blind, placebo-controlled study of the effect of probiotics on the gut microbiome of patients with gastro-oesophageal reflux disease treated with rabeprazole

**DOI:** 10.1186/s12876-022-02320-y

**Published:** 2022-05-20

**Keywords:** GERD, Probiotics, Proton pump inhibitors, Gut microbiome

## Abstract

**Background:**

For patients with gastro-oesophageal reflux symptoms, the preferred treatment is proton pump inhibitor (PPI) administration for approximately 8 weeks. However, long-term use of PPIs can cause gut microbiome (GM) disturbances. This study is designed to evaluate the effect of probiotics combined with a PPI on the GM and gastrointestinal symptoms of patients with gastro-oesophageal reflux disease (GERD).

**Method:**

This is a randomized, double-blind, placebo-controlled trial. A total of 120 eligible patients with GERD will be randomized into the experimental group or the control group. The treatment includes two phases: the initial treatment period lasts 8 weeks (weeks 1–8), and the maintenance treatment period lasts 4 weeks (weeks 9–12). During the initial treatment period, the experimental group will take rabeprazole and LiHuo probiotics, and the control group will take rabeprazole and a probiotic placebo; during the maintenance treatment period, the experimental group will take LiHuo probiotics, and the control group will take a probiotic placebo. The primary measure is the change in the GM. The secondary measures are the Reflux Disease Questionnaire (RDQ) score, Gastrointestinal Symptom Rating Scale (GSRS) score, faecal metabolome (FM), body mass index, Los Angeles grade of oesophagitis, adverse event (AE) rate and treatment compliance. Each outcome indicator will be assessed at day 0 (before administration), day 28 and/or 56 (during administration), and day 84 (end of administration) to reveal intragroup differences. AEs will be monitored to assess the safety of LiHuo probiotics.

**Discussion:**

This will be the first trial to use the intestinal flora metagene method to analyse the effects of probiotics on patients with GERD receiving long-term PPI treatment. The goal is to provide evidence for the use of probiotics to reduce intestinal flora disorders and other symptoms of gastrointestinal discomfort in patients with GERD who have used PPIs for a long period.

***Trial registration*:**

Chinese Clinical Trial Registry (ChiCTR) (NO. ChiCTR2000038409). Registered on November 22, 2020, http://www.chictr.org.cn/showproj.aspx?proj=56358.

**Supplementary Information:**

The online version contains supplementary material available at 10.1186/s12876-022-02320-y.

## Background

With the widespread availability of proton pump inhibitors (PPIs) in digestive diseases, PPIs are used in the treatment of GERD and gastric or duodenal ulcers and as part of *Helicobacter pylori* eradication. PPIs are the most widely prescribed class of drugs in the United States. In 2012, 14.9 million United States patients received 157 million prescriptions [1]. From 2006 to 2010, PPIs accounted for more than $10 billion in estimated annual healthcare costs in the United States [2]. Based on the French National Health Data System (SNDS), there were 15,388,419 people who used PPIs at least once in 2015, accounting for 29.8% of the French adult population. The average treatment time was 40.9 days, but 4.1% of users received continuous PPI treatment for more than 6 months [3]. GERD refers to the reflux of gastroduodenal contents into the oesophagus that causes symptoms such as acid reflux and heartburn. Global population-based research results show that the prevalence of GERD ranges from 2.5% in China to 51.2% in Greece [4]. The prevalence of GERD symptoms occurring at least once a week is 13% and is higher in Western countries [5]. The prevalence of GERD symptoms in the Asia–Pacific region is increasing [6]. In a survey of 71,812 American participants, 32,878 (44.1%) people had experienced GERD symptoms in the past, and 23,039 (30.9%) people had experienced GERD symptoms in the past week; 35.1% of people who had symptoms of GERD were currently receiving medication (55.2% of them used PPIs). Among the 3229 participants who took PPIs, 54.1% had persistent GERD symptoms [7].

Moderate alterations to the upper and distal gut microbiota were observed in patients who used PPIs [8], and changes in the microbiota of the gastrointestinal tract are also associated with PPIs. Previous studies have shown that PPI use results in an increase in multiple taxa from the orders *Lactobacillales* (e.g., *Enterococcaceae* and *Streptococcaceae*) and *Bacillales* (e.g., *Staphylococcaceae*), as well as from the families *Pasteurellaceae* and *Enterobacteriaceae,* and a decrease in the families *Bifidobacteriaceae*, *Ruminococcaceae*, and *Lachnospiraceae* and the class *Mollicutes*. PPIs have the most significant impact on the microbiota in addition to antimicrobials according to the literature [9]. A study indicated that the GM of rheumatoid arthritis (RA) patients who were receiving PPIs was different, as *Streptococcus* was enriched in RA patients who received PPIs. The gut microbiota of PPI users could be modified by the production of virulence factors. This featured microbial function was positively correlated with the relative abundance of *Streptococcus* [10]. Frequent use of PPIs was associated with an increased risk of RA in women, with a higher risk observed in people with a longer PPI treatment period [11]. Researchers of one team observed positive effects of a multispecies probiotic in patients undergoing long-term PPI therapy. The richness of *Stomatobaculum* in the microbiome was decreased and that of *Bacillu*s increased during the intervention, and gastrointestinal quality of life simultaneously showed significant improvements. However, only sparse evidence can support the routine use of probiotics during PPI therapy [12].

In a clinical study on children, the incidence of gut microbial dysbiosis in children treated with PPIs combined with probiotics was only 6.2%, and 56.2% of children who used PPIs and placebo after 12 weeks developed gut microbial dysbiosis. Taking probiotics reduces the incidence of gut microbial dysbiosis in children receiving PPI treatment [13]. Additionally, probiotics can significantly reduce the frequency of reflux, promote gastric emptying, and improve reflux symptoms in infants [14, 15].

In a systematic review on the association between GERD and probiotics, five of eleven studies indicated that probiotics are beneficial for reflux symptoms; three studies indicated that probiotics can reduce reflux symptoms; one study reported probiotic-induced improvements in reflux or heartburn; dyspepsia symptoms improved in five studies; and other upper gastrointestinal symptoms were improved in nine studies, with such symptoms including nausea (three studies), abdominal pain (five studies), and gas-related disorders (four studies) such as belching, gurgling, and burping. Probiotics can effectively reduce the frequency and severity of reflux, heartburn and dyspepsia in adults suffering from GERD [16]. In the observation of reflux oesophagitis, compared with patients using placebo and esomeprazole, patients who use probiotics combined with esomeprazole for 8 weeks have significantly lower Gastrointestinal Symptom Rating Scale (GSRS) diarrheic comprehensive scores and a significantly higher negative rate of small intestinal bacterial overgrowth [17].

However, there are still few clinical studies on adult gastro-oesophageal reflux patients who use PPIs and probiotics to improve their symptoms compared with those who use a PPI only, and there is no study comparing PPI treatment alone and PPI treatment combined with probiotics in terms of the analysis of intestinal microbiota by metagenomics. Therefore, this study is designed to observe the change in reflux symptoms, the gastrointestinal symptoms of patients with long-term use of PPIs, the metagenomic change in intestinal microbial, and the change after probiotic intervention.

## Methods and design

### Design

This is a randomized, double-blind, placebo-controlled clinical trial. The protocol was prospectively registered in the Chinese Clinical Trial Registry (ChiCTR) (No. ChiCTR 2,000,038,409) (Additional file 1: Appendix 1) and approved by the Ethics Committee of the First Affiliated Hospital of Nanchang University (Approval No. IIT [2020] EC 003-2) (Additional file 1: Appendix 2). This protocol was developed based on the Standard Protocol Items: Recommendations for Interventional Trials (SPIRIT). The study process is shown in Fig. 1.

**Fig. 1 Fig1:**
[figure not shown]
Flow chart of the protocol

### Volunteer recruitment

Posters will be disseminated at the hospital to recruit participants. During their appointment at the Department of Gastroenterology in the First Affiliated Hospital of Nanchang University, volunteers who are interested in the study will undergo preliminary evaluations based on the inclusion and exclusion criteria. Additionally, the investigator will explain the purpose, process, and potential benefits and risks of this study, and the volunteers may choose to participate by signing the informed consent form. Next, the volunteers will undergo further screening to determine their eligibility. Eligible participants will receive the study intervention and follow-up. The following steps describe the formal intervention and follow-ups (Table 1).

**Table 1 Tab1:** Study and follow-up schedule

Item^1,10^		Screening	Baseline	Initial treatment		Maintenance treatment
		Visit 0	Visit 1	Visit 2	Visit 3	Visit 4
		Days −3 to 0	Day 0	Week 4	Week 8	Week 12
Basic demographics		X				
Vital signs, physical examination		X				
Allergies, medical history^2^, medication history^3^, surgical history^4^		X				
Smoking and drinking		X				
Gastroscopy		X^5^				X^6^
Abdominal ultrasound B^7^		X				
Serum human chorionic gonadotropin (hCG)		X				
ECG		X				X
Blood test, urine analysis, stool test (including occult blood)		X				X
Liver/kidney function^8^		X				X
Signed informed consent		X				
Inclusion/exclusion criteria verification			X			
Primary outcome measure	GM^11^ (metagenomics)	X		X	X	X
Secondary outcome measures	RDQ	X	X	X	X	X
	GSRS		X	X	X	X
	Faecal metabolomics^11^	X		X	X	X
	BMI ^9^		X	X	X	X
	LA grade	X				X
Safety measures	AEs			X	X	X
	SAEs			X	X	X
Compliance verification			X	X	X	
Concomitant medications		X	X	X	X	

^1^Visit window: 0 days for visit 1; ± 2 days for visits 2, 3, and 4

^2^Medical history: current and past illnesses, including peptic ulcer, gastritis, oesophagitis, cardiovascular and cerebrovascular diseases, cancer, and mental illness

^3^Medication history: PPI, histamine H2 antagonists, antibiotics, probiotics, prokinetics, gastric mucosal protectors, and other drugs for gastro-oesophageal reflux (including herbs)

^4^Surgical history: gastrointestinal surgeries, including gastro-oesophageal and duodenal surgeries

^5^Performance of gastroscopy in domestic tertiary or higher hospitals in the past 3 months

^6^Gastroscopy at visit 4, LA grades at visit 0 and visit 4 referring to patients with oesophagitis (LA-A, LA-B or LA-C)

^7^Abdominal ultrasound B: to examine the abdominal organs to screen for upper abdominal malignancies

^8^Liver and kidney tests: ALT, AST, total bilirubin, blood urea nitrogen, Scr

Weight and height will be measured in the morning

^10^For the abdominal B-ultrasound and ECG evaluations performed at visit 0, examination results from the past 3 months are acceptable; examination results from the past 1 week are acceptable for blood HCG, blood, routine urine and stool (including occult blood) tests, and liver/kidney function tests

^11^The detection of GM will be conducted within 2 months after the end of the follow-ups, and the detection of FM will be performed within 2 months of when data analysis determines that the probiotics have a significant effect on GM

### Inclusion criteria

Consenting (Additional file 1: Appendix 3) patients with GERD or one of its signs after gastroscopy:In the past 3 months, gastroscopy performed at domestic tertiary hospitals has shown oesophagitis (LA-A, LA-B or LA-C);In the past 3 months, gastroscopy performed at domestic tertiary hospitals has not revealed oesophagitis, but there are symptoms such as heartburn, acid reflux, and poststernal burning pain; in addition, the RDQ score is ≥ 12 [18];
The subject’s age is 18–65 years (inclusive), male or female.

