### Secondary outcome

RDQ score: The RDQ (see Additional file 1: Appendix 5) includes 4 symptoms: heartburn, acid reflux, regurgitation, and noncardiac chest pain. Each symptom is rated on a 0–5 scale based on its frequency and severity in the last week. The total score is 40, and a higher score is associated with more severe symptoms. RDQ ≥ 12 indicates GERD [18, 21]. The RDQ will be used to evaluate reflux-related symptom scores on day 0 (week 0), day 28 (week 4), day 56 (week 8), and day 84 (week 12).GSRS score: The GSRS (see Additional file 1: Appendix 6) is a self-rating scale that includes 15 items in 5 subscales (abdominal pain, acid reflux, dyspepsia, constipation, and diarrhoea). Each item is rated on a Likert scale ranging from 0–3 (none, mild, moderate, mild) based on the severity of symptoms in the last week. The total score is 45, and a higher score is associated with more severe symptoms [22–24]. The GSRS will be used to evaluate gastrointestinal disease symptom scores on day 0 (week 0), day 28 (week 4), day 56 (week 8), and day 84 (week 12).Faecal metabolome (FM): Based on the faeces, FM from day 0 (week 0), day 28 (week 4), day 56 (week 8), and day 84 (week 12) will be evaluated. Stool samples will be extracted using the protein precipitation method, and the supernatant will be transferred to sample vials for mass spectrometry combined with liquid chromatography (LC–MS/MS) analysis. The original data will be subjected to peak alignment, retention time correction, and peak area extraction through the XCMS-Plus program. The structure of metabolites will be identified by accurate mass matching (< 5 ppm) and two-level spectrum matching, and the METLIN database will be retrieved. Missing values > 50% in the group will be deleted, and the data will be normalized. Multidimensional statistical analysis will then be carried out, including unsupervised principal component analysis (PCA), supervised partial least squares discriminant analysis (PLS-DA) and potential differential metabolite analysis. Metabonomic analysis could further identify the potential differential metabolites of probiotics in the treatment of GERD, and correlation analysis between the gut microbiota and metabolites could be performed.Change in the Los Angeles (LA) grade of oesophagitis: According to gastroscopy, the change in the LA grade of oesophagitis will be evaluated.Body mass index (BMI): BMI = weight (kg)/height (m)^2^. BMI will be measured in the morning using the same weight and height scales at each visit. Participants will be instructed to wear light clothing and take off their shoes (standing barefoot or wearing socks no thicker than 0.1 cm) during the weight and height measurements.AE rate: all the AEs collected as described below will be used to calculate the AE rate in each group.Treatment compliance will be monitored as described in the “Volunteer compliance monitoring” section. Although efforts have been made to promote treatment compliance, there may still be differences between the two groups due to AEs.

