### Statistical analysis

First, the intention-to-treat (ITT) analysis will be conducted between the two groups, including all the intended participants who do or do not complete the follow-up. Then, per-protocol (PP) analysis will be conducted in the four-subgroup datasets according to compliance (100%, ≥ 80%, 60–80%, and < 60%) to validate the robustness of the results. The datasets will be analysed as described below.

With a randomized block design, the nonparametric rank sum test and Friedman M test will be performed to analyse the difference in each outcome measure at each time point (see “Intervention Outcome Measures” for details) between the two groups, including the GM analysis, RDQ score, GSRS score, faecal metabolomics, and BMI. The significance level will be set to *P* = 0.05. Next, the paired Wilcoxon signed-rank test will be performed for pairwise intragroup comparisons to analyse the change trends for each outcome measure before, during, and after the probiotic intervention. The significance level will be set at *P* = 0.05/[k(k-1)/2], where k is the number of groups in the comparison. For analysis of the oesophagitis grade, the diagnosis of LA-B at baseline and LA-A at week 12 indicates that the patient's oesophagitis grade will have decreased by one level. If the grade is LA-C at baseline and LA-A at 12 weeks, the patient’s oesophagitis grade will have decreased by 2 levels. The number of oesophagitis grades reduced by 1 and 2 levels in each group will be calculated. Then, a chi-square (*χ*^2^) test will be performed. AE rates in the two groups will be compared by the *χ*^2^ test or Fisher’s exact probability test based on the occurrence frequency of AE, and the difference in treatment compliance will be also examined by the *χ*^2^ test.

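### The RDQ comparison between arms ignores baseline RDQ although the entry criteria allow it to vary widely; a baseline-adjusted test would recover sensitivity on this secondary outcome at almost no cost

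*Protocol article*

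**What the plan says.** Under Inclusion criteria, a patient qualifies by either of two routes.

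- **Oesophagitis:** "In the past 3 months, gastroscopy performed at domestic tertiary hospitals has shown oesophagitis (LA-A, LA-B or LA-C". No symptom or RDQ minimum is attached.
- **No oesophagitis:** gastroscopy "has not revealed oesophagitis, but there are symptoms such as heartburn, acid reflux, and poststernal burning pain; in addition, the RDQ score is ≥ 12".

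Under Secondary outcome, RDQ is scored as follows: "The total score is 40, and a higher score is associated with more severe symptoms. RDQ ≥ 12 indicates GERD". The Abstract lists RDQ first among the secondary measures. Table 1 schedules it at screening (Visit 0), at day 0 before treatment (Visit 1), and at weeks 4, 8 and 12.

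Under Statistical analysis, "the nonparametric rank sum test and Friedman M test will be performed to analyse the difference in each outcome measure at each time point" between the two groups, and RDQ is named among the measures. No baseline covariate or stratum is stated for this comparison. The section mentions a randomised block design but names no blocking factor, and Randomization and blinding describes no stratified allocation. The one stated use of baseline is the signed-rank test within each arm, which does not compare the arms.

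**The concern.** The criteria admit oesophagitis patients below the protocol's own symptom cut-off, down to a score of 0, alongside patients who must score at least 12. If a fair number start low, follow-up RDQ becomes a mixture of low and high scorers. Much of its spread then reflects where patients began rather than which arm they are in. A rank sum test on follow-up scores alone has to find the treatment difference through that spread, although the score that explains it is recorded before treatment.

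Low scores are plausible under the text. The qualifying gastroscopy may be three months old, GERD drugs are excluded only for the last two weeks, and RDQ covers only the last week. At stake is the chance of detecting a real symptom benefit on the first-listed secondary outcome; the Background names change in reflux symptoms among the study's aims.

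**Working it through.** **1. The plan's own figure.** The Sample size section gives a Chao1 difference of 145, SD 230, alpha 0.025 and beta 0.20. With alpha taken as two-sided,

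n = 2 × (2.241 + 0.842)² × (230/145)² = 47.83 per arm, against the stated 47.9.

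For Shannon's index (difference 0.9, SD 0.8) the same formula gives 15.02, against 15.0. The sample size is reproduced and does not involve RDQ, so nothing below alters it or the power for the primary outcome. The article gives no RDQ effect, SD or power.

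**2. Inputs for RDQ.** From the document: 60 per arm and 20% loss, so 60 × (1 − 0.20) = 48 completers per arm; score range 0–40; cut-off 12; test level 0.05. Assumed, because the document gives nothing: low scorers have a mean baseline of about 5 and the others about 20; follow-up = baseline × Beta(2,3) × (1 − 0.3 in the probiotic arm) + N(0, SD 2), bounded at 0 and 40. The share below 12 is also assumed: oesophagitis share × share of those with RDQ < 12 (for example 0.3 × 0.3 = 9%; 0.7 × 0.6 = 42%).

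**3. Tests compared.** The planned rank sum test on all patients is set against the van Elteren test with strata Visit 1 RDQ < 12 and ≥ 12:

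T = Σ[(W_h − E_h)/(N_h + 1)] / √Σ[V_h/(N_h + 1)²],

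where, in stratum h, W_h is the rank sum of the probiotic arm, E_h and V_h are its null mean and variance, and N_h is the number of patients.

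**4. Power by simulation.** Two runs used different baseline distributions with the means above.

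| Share with RDQ < 12 | Run 1: planned vs stratified | Gain | Run 2: planned vs stratified | Gain |
|---|---|---|---|---|
| 9% (0.3 × 0.3) | 59% vs 65% | 6 | 55% vs 62% | 7 |
| 15% (0.5 × 0.3) | 53% vs 61% | 8 | 53% vs 60% | 7 |
| 18% (0.3 × 0.6) | 49% vs 58% | 9 | 50% vs 58% | 8 |
| 21% (0.7 × 0.3) | 47% vs 56% | 9 | 46% vs 57% | 11 |
| 30% (0.5 × 0.6) | 39% vs 52% | 13 | 38% vs 53% | 15 |
| 42% (0.7 × 0.6) | 32% vs 45% | 13 | 30% vs 46% | 16 |

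At small shares the gain fades: 65% vs 68% at 5%, 66% vs 67% at 3%, and 70% vs 70% at 0%. If the low scores lie just under the cut-off (spread over 6–12), it is 62% vs 66% at 9% and 61% vs 66% at 15%. Type I error of the stratified test is 4–5%.

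**5. What stratifying does and does not recover.** At a 42% share the stratified test reaches 45–46%, still well below the roughly 70% seen with no low scorers. Part of the loss arises because low scorers have less to gain, and no analysis of all patients removes that part. Stratifying recovers only the part due to spread between patients.

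**The case against.** The strongest case against is that this is a matter of efficiency on a secondary outcome, not an error. The rank sum test on randomised arms is valid, no RDQ power was promised, and baseline strata are often left to an analysis plan that is not shown. The first two points stand and set the size of the finding. The third does not dispose of it: the article names the test to be used, and the comment is on that stated test.

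Several stronger readings are tempting, and the document does not support them.

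- **That many oesophagitis patients will have little or no reflux score.** The criteria only permit this. Neither the oesophagitis share nor those patients' RDQ is given. Volunteers are recruited while attending a gastroenterology department and off GERD drugs for two weeks, which may favour symptomatic patients.
- **That low scorers carry no information, or overwhelm the effect.** Rabeprazole is given in both arms only to week 8, so a low scorer can worsen by week 12 and the arms can separate. In the simulation the mean difference falls only from 2.4 to 2.1 at a 15% share. At 42% it keeps 1.62/2.42 = 0.67 of its size, more than the 1 − 0.42 = 0.58 that simple proportional dilution would predict.
- **That the pooled result describes the wrong patients.** The Inclusion criteria cover GERD or one of its signs at gastroscopy, so the pooled result describes the population enrolled.
- **That the RDQ ≥ 12 stratum should become the main estimate.** The article puts intention-to-treat first, and this would place a subgroup above it. A patient who met the threshold at screening could also score below 12 at Visit 1 and drop out of the headline result.

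**Conclusion.** The point holds as a free improvement. The entry criteria allow a wide range of baseline RDQ, and the stated between-arm test leaves that information unused. The consequence is lost sensitivity on one secondary outcome. There is no bias, and the primary outcome and the sample size are untouched.

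The loss against a baseline-stratified test is 0 points with no low scorers, about 3 at a 5% share and up to about 15 at 42%. It rests on an assumed 30% relative reduction, on assumed baseline scores and above all on the unknown share below 12. In none of the scenarios examined did the stratified test have less power than the planned one.

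**What to change.** Leave eligibility as it is, and keep the all-patient intention-to-treat comparison as the main RDQ result. Replace the unadjusted rank sum test for RDQ with one of the following, chosen and written down before unblinding:

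- a van Elteren test stratified by Visit 1 RDQ (< 12 versus ≥ 12); or
- a rank analysis of covariance on Visit 1 RDQ, which avoids dependence on a single cut-off.

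Report the number and share in each arm with Visit 1 RDQ below 12, so that readers can judge how much the point matters. Give the between-arm result in the RDQ ≥ 12 stratum only as a prespecified supportive result.

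The cost is a sentence or two in the analysis section. The score is already collected before treatment, no patient with follow-up data leaves the comparison, and if nobody starts below 12 the van Elteren test reduces to the planned rank sum test. Timing matters: chosen after unblinding, the stratum result would be a post hoc subgroup.
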